### Follow up

Once included in the study, and during hospital stay, patients will be daily evaluated by at least one of the investigators. After discharge, patients will be instructed to measure their temperature twice a day, and to contact their doctors if it is above 38 °C, or in case of shivering. During the 6 months period after randomization, all patients included in the study will be periodically assess by the investigator in the follow-up visits (Table 3) that will include physical examination, blood tests, blood cultures and TEE.

**Table 3 Tab3:**
[figure not shown]
Study flow diagram

### Sample size

This study was designed as a non-inferiority trial. Most IE complications occur in the initial phase of the disease, usually in the first week. In previous studies, 6-months all-cause mortality ranged from 18 to 26% [7, 12]. Based on results and survival curves from these studies, we estimate a 2 to 5% risk of all-cause mortality after randomization. The need for unplanned surgery was estimated between 1 and 3% [12], the risk of new clinical embolic events between 1 and 2% [7], and the risk of relapse between 1 and 3% [7, 21, 22]. Thus, the risk of the primary outcome was estimated to be between 5 and 10%.

Considering a 10% composite event rate [7], selecting a non-inferiority margin of 10 percentage points, a power of 80% to confirm non-inferiority, a one-sided confidence interval of 97.5%, and assuming a 5% loss to follow-up, the number of patients to be included is 298.

### Present status

The first patient in SATIE trial will enrolled in in May 2020. The end of enrollment is projected for September 2021.

### Statistical analysis

Categorical variables will be expressed as a frequency and a percentage, and compared with the chi-square test and the Fisher exact test when necessary. Quantitative variables will be expressed as median and interquartile range or mean and standard deviation. Assessment of normality and equality of variances for continuous data will be performed using the Shapiro-Wilk test and the Levene test, respectively. Thereafter, continuous variables will be compared by a Student t-test, Mann-Whitney U test or Fisher-Pitman permutation test as necessary. First, baseline variables in both groups (control and experimental) will be compared by a chi-square test or Student t-test. If any of the variables is found to be asymmetrically distributed, the effect of the variable will be adjusted in each of the endpoints.

Endpoint analysis: Primary endpoint: differences in the primary outcome will be assessed by the evaluation of absolute and relative risk differences between both groups, calculating the confidence interval (CI) of the difference to assess non inferiority. To evaluate the impact of the intervention in the risk of each of the events included in the composite endpoint, the relative risk with 95% CI will be used, adjusted or not for potential confounding variables asymmetrically distributed, as previously expressed. Alternatively, we will also evaluate differences considering time, calculating the CI of the differences in survival free from the composite endpoint by means of Kaplan Meier curves. Secondary endpoints. 1st: to compare the mean change in the score of SF-12 questionnaire for perceived quality of life between the time of randomization and 4 weeks later, a MANOVA analysis will be used; 2nd: to compare the mean change in the score of the SPPB for functional performance between the time of randomization and 4 weeks after, a MANOVA analysis will be used; 3rd: to compare the median of total hospital stay six months after inclusion a non-parametric test will be used; 4rd: to compare the incidence of clinical complications related to prolonged hospital stay during the six months after inclusion, the risk ratio with its 95% CI will be used.

All analyses will be performed by intention-to-treat and by per-protocol. Stratified analyses of primary and secondary endpoints by the following pre-specified subgroups will be performed: age, sex, diabetes mellitus, chronic renal failure, native vs prosthetic valve IE, surgery vs medical treatment, and microorganisms (streptococci, enterococci, coagulase-negative staphylococci, *Staphylococcus aureus*).

All tests will be two-sided, and differences will be considered statistically significant at *P*-values < 0.05. Statistical analysis was performed with Stata V.12.0 (StataCorp, College Station, Texas, USA).

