### Intervention

Patients will be included in the study consecutively. We will prospectively register all patients that will not be included in the study, specifying the reason. All the information will be recorded in an electronic case record form (RedCap). Patients treated for at least 10 days of appropriate parenteral antibiotic therapy overall (according to guidelines and microbiology sensitivity testing), and at least 7 days of parenteral antibiotic therapy after valve surgery when indicated, fulfilling all inclusion criteria and who do not meet any exclusion criteria, once having signed the informed consent form, will be randomized to one of the two intervention groups:
Experimental group: patients allocated to this group will receive a short course of antibiotic therapy for 2 weeks.Control group: those patients allocated to continue with standard parenteral treatment will maintain antibiotic treatment for 4 to 6 weeks.

In all operated patients, valve culture will be systematically performed; in case of positive valve culture, the day of the surgery will be considered the first day of antibiotic treatment.

Randomization will be performed with blocks of 4 and 6 patients by an automated assignment system with a ratio of 1:1. In addition, randomization will be further stratified by the need of cardiac surgery using RedCap.

Criteria for discontinuing allocated interventions include: need for starting chemotherapy or immunosuppressive therapy during intervention, patients’ inability to continue follow-up after being discharged from hospital, and emergence of any exclusion criteria, except for pregnant women once antibiotics’ administration has ended.

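### Adjustment covariates are chosen by baseline significance tests, so chance decides the model and it is unclear which interval is compared with the 10-point margin

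*Protocol article*

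**What the plan says.** All references are to the protocol article.

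- **Statistical analysis, baseline step:** "First, baseline variables in both groups (control and experimental) will be compared by a chi-square test or Student t-test". The next sentence gives the consequence: "If any of the variables is found to be asymmetrically distributed, the effect of the variable will be adjusted in each of the endpoints".
- **Statistical analysis, threshold:** "All tests will be two-sided, and differences will be considered statistically significant at" P-values below 0.05. The adjustment sentence has no threshold of its own, so this general one is the natural reading.
- **Statistical analysis, primary endpoint:** "differences in the primary outcome will be assessed by the evaluation of absolute and relative risk differences between both groups", with a confidence interval of the difference to judge non-inferiority. No covariate is mentioned.
- **Statistical analysis, components of the composite:** relative risks with 95% CI, "adjusted or not for potential confounding variables asymmetrically distributed, as previously expressed".
- **Intervention:** patients are allocated 1:1 by an automated system, in blocks of 4 and 6. On strata the section says: "randomization will be further stratified by the need of cardiac surgery using RedCap".

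No covariate is fixed in advance. Surgery enters only as a randomisation stratum and a subgroup. Age, valve type and microorganism enter only as subgroups.

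**The concern.** Allocation is randomised, blocked and automated, so a baseline difference between arms is a chance difference. A P-value for it says nothing about whether the variable predicts death, surgery, embolism or relapse. The rule can bring in an irrelevant variable at P = 0.04 and leave out a strong predictor at P = 0.20. A stratified factor is the least likely of all to trigger.

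Two things are at stake. First, the covariate set is unknown until the baseline data have been tested, and any precision from known prognostic factors is gained only by accident. Second, the general sentence reaches every endpoint while the primary-endpoint sentence describes a plain risk difference. A reader therefore cannot tell whether the adjusted or the unadjusted interval is held against the margin. This is a stated method, not a detail left to the SAP: a SAP that followed the article would carry the same rule.

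**Working it through.** **1. The plan's own figure.** The Sample size section gives: "Considering a 10% composite event rate [7], selecting a non-inferiority margin of 10 percentage points, a power of 80% to confirm non-inferiority", one-sided 97.5% confidence, 5% loss, 298 patients. Assume 10% in both arms.

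n per arm = [2 × 0.10 × 0.90] × (1.960 + 0.842)² / 0.10² = 141.3.

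The total is 2 × 141.3 = 282.6, rounded up to 283, and 283 / 0.95 = 298. Rounding each arm up first gives 284 / 0.95 = 299. The stated size reproduces, and this point does not change it.

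**2. How often chance triggers adjustment.** For k independent baseline variables tested at 0.05 under correct randomisation, P(at least one) = 1 − 0.95^k and the expected number is 0.05k. The article does not list the baseline variables, so k is assumed. The value 7 equals the number of subgroup factors it names.

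| k | P(at least one trigger) | Expected triggers |
|---|---|---|
| 7 | 30% | 0.35 |
| 10 | 40% | 0.5 |
| 20 | 64% | 1.0 |
| 30 | 79% | 1.5 |

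**3. Why the surgery stratum tends to be missed.** A block of 6 holds 3 patients per arm, so an unfinished block can leave the arms at most 3 apart within one randomisation list. Balance on surgery is close by construction, and its baseline test will rarely fall below 0.05.

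**4. Events available.** With about 141 evaluable patients per arm:

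- Primary endpoint: 141 × 0.10 = 14.1 per arm, about 28 in all. Treatment plus one covariate leaves 28 / 2 = 14 events per parameter; treatment plus two leaves 28 / 3 ≈ 9.
- Components: the Sample size section puts the individual risks between 1% and 5%, so 141 × 0.01 = 1.4 to 141 × 0.05 = 7.1 events per arm.

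**5. Effect on the non-inferiority conclusion.** A simulation used 142 per arm, 8,000 runs per scenario, 7 balanced binary covariates of which one was prognostic, a linear risk model and robust intervals. Non-inferiority was declared when the upper limit was below 10 points. Type I error was taken at 10% versus 20%, and power at 10% in both arms.

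| Prognostic factor | Quantity | Unadjusted | Prespecified | Test-triggered |
|---|---|---|---|---|
| Moderate (risk 5% vs 15%) | Type I error | 2.8% | 2.9% | 2.7% |
| Moderate | Power | 81.4% | 81.9% | 81.3% |
| Strong (risk 2% vs 18%) | Type I error | 2.6% | 2.6% | 2.6% |
| Strong | Power | 80.8% | 83.3% | 80.8% |

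The Monte Carlo standard error of a 2.5% rate is √(0.025 × 0.975 / 8,000) = 0.17 points, so the type I error columns do not differ in any way that matters. Against prespecified adjustment, the rule forgoes 0.6 points of power (81.9 − 81.3) with the moderate factor and 2.5 points (83.3 − 80.8) with the strong one. Triggered and unadjusted analyses reached opposite conclusions in about 0.4% of trials at the margin and in 1.5% to 1.7% with no true difference.

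A second simulation, with three moderate prognostic factors and no true difference, put that disagreement at 1.3% (k = 7), 3.1% (k = 20) and 4.0% (k = 30). At k = 30, power was 79.1% with the rule, 80.6% unadjusted and 81.0% prespecified. If the more favourable of the two intervals could be taken, type I error at the margin rose from 2.4–2.6% to 2.6–2.9%.

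**The case against.** The strongest reply is that the rule does little damage. An unadjusted comparison in a randomised trial is valid, the trigger looks at baseline data and not at outcomes, and read with the 0.05 threshold it is largely mechanical. All of that stands, and it rules out four stronger readings that a reader might infer.

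- **That the error rate of the interval fails.** The simulations do not show this. Type I error under the rule matches that of the unadjusted and prespecified analyses.
- **That the model may be chosen by its result.** The text does not allow this. The model depends on baseline data. What freedom exists comes from not saying which interval decides, and even taking the better one moved the error only slightly.
- **That the option to adjust or not is written into the primary analysis.** That phrase belongs to the component relative risks. Adjustment reaches the primary endpoint only through the general sentence.
- **That the primary model would be overfitted.** About 28 events can carry the one or two covariates usually triggered. Sparse data is a concern for the components only.

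It can also be said that the 30% to 79% measures how often the trigger fires, not harm, and that it rests on an assumed number of independent variables. That is right, and the figure should be read so.

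What the reply does not answer is that a significance test is a poor way to choose covariates under randomisation, or that the two sentences leave the deciding analysis open.

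**Conclusion.** The point holds as a fault in how the analysis is specified, with modest numerical consequences; it should be fixed. The rule selects covariates by chance imbalance, tends to omit the one factor the design itself stratifies on, and leaves unclear whether an adjusted or an unadjusted interval is set against the 10-point margin.

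Its size is a 30% to 79% chance that adjustment is triggered, up to about 2.5 points of power forgone, and roughly 0.4% to 4% of trials in which the two analyses disagree, without material inflation of type I error. Component models, at about 1.4 to 7 events per arm, are too sparse to take several triggered covariates.

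These figures assume 7 to 30 independent baseline variables, a 0.05 trigger, a 10% event rate in the control arm, and the simulated strengths of prognosis. The article gives neither the number of baseline variables nor the prognostic strength of any of them.

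**What to change.** 1. Delete the baseline significance tests and the sentence that triggers adjustment. Describe baseline by arm without P-values.
2. Name one primary non-inferiority analysis: the risk difference with its confidence interval, adjusted for the surgery stratum, compared with the 10-point margin.
3. Prespecify one sensitivity analysis that adds a short list of covariates already collected and chosen for prognosis (for example age, native or prosthetic valve, microorganism). Report it as a standardised risk difference so that it can be read against the same margin.
4. Report the component relative risks unadjusted.

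Adjusting for surgery gains precision only so far as surgery predicts outcome, which the article does not quantify. The sure gain is that the deciding analysis is fixed. The cost is wording in the protocol or SAP, settled before outcome data are examined, and slightly more analysis work. No extra data are needed and the sample size stays at 298.

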### Endpoints

The primary endpoint is a composite of all-cause mortality, unplanned cardiac surgery, clinical embolisms, and relapses within 6 months after the inclusion.

Unplanned cardiac surgery is defined as heart surgery not planned before randomization. Surgery due to sterile pericardial effusion or hemorrhage is not included. Clinical embolisms are defined as any symptomatic embolic event that occurs after randomization. Relapse has been defined as the appearance of any positive blood culture with the same primary microorganism or the progression or reappearance of typical echocardiographic findings of IE (new appearance or enlargement of a vegetation, appearance of new periannular complications) documented by transesophageal echocardiography (TEE).

Secondary objectives include the evaluation of the economic consequences and the impact on patients’ experienced quality of life, functional performance, and complications related to prolonged hospital stay (Table 2).

**Table 2 Tab2:** Secondary endpoints

Perceived quality of life. We will measure changes in the mean score of SF-12 between the time of randomization and 4 weeks after.	
Functional performance. We will measure changes the change in the mean score of short performance physical battery test (SPPB) between the time of randomization and 4 weeks after.	
Risk of clinical complications related to prolonged hospital stay (nosocomial infections, intravascular catheter-related infections) in the next 6 months after the inclusion in the study.	
Total hospital length of stay in the next 6 months after the inclusion in the study, including admissions related or not related to IE.	
Total costs related with patients’ treatment in the next 6 months after the inclusion in the study.	

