### Limitations

Despite being a randomized clinical trial, the design is open-label. In any case, the variables included in the composite endpoint (death, relapse, unplanned cardiac surgery, symptomatic embolisms) can be objectively measured, reducing the risk of information bias. In addition, in order to minimize biases, investigators recruiting patients will be blinded to the randomized sequence, to avoid the possibility of patients selection for an specific arm, and the evaluation of adverse events will be supervised by an independent committee that will not know which group the patient belongs to.

The sample size may not guarantee the statistic power necessary to detect statistical significant differences in some of the secondary endpoints.

Randomization may not prevent the presence of confounding factors in variables that may not be measured, may not be equally distributed between the two groups, or may have a small marginal distribution but significant impact in the measured effects. External validation may be compromised, as the study will be carried out in reference centres for the treatment of IE, and due to the restrictions of the inclusion and exclusion criteria. The study will not be able to analyse potential clinical events of interest that occur beyond 6 months.

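### SF-12 and SPPB change are assigned to MANOVA; a prespecified ANCOVA with the baseline score as covariate would give an adjusted mean difference with CI and better precision than the change score, from data already collected

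*Protocol article*

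**What the plan says.** Table 2 (Endpoints) defines quality of life as a change over four weeks: "We will measure changes in the mean score of SF-12 between the time of randomization and 4 weeks after". Functional performance on the SPPB is defined in the same way.

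The Statistical analysis section then fixes the method. The SF-12 comparison is made "between the time of randomization and 4 weeks later, a MANOVA analysis will be used", and the SPPB comparison "between the time of randomization and 4 weeks after, a MANOVA analysis will be used". It does not say which variables form the multivariate response.

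The only route by which a baseline score could enter as a covariate is a general rule applied after baseline testing: "If any of the variables is found to be asymmetrically distributed, the effect of the variable will be adjusted in each of the endpoints".

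In the same section, the primary endpoint gets a confidence interval for the difference, and both the components of the composite and the hospital-stay complications get a risk ratio with 95% CI. SF-12 and SPPB get a test only. The Limitations section concedes: "The sample size may not guarantee the statistic power necessary to detect statistical significant differences in some of the secondary endpoints".

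**The concern.** Each of these endpoints is the change in a score between two occasions. MANOVA is designed for several outcomes taken together, so the named method does not match the endpoint, and its meaning depends on a response vector that the text leaves open. The readings give different tests and different power.

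The Background and Discussion present better quality of life and functional recovery as main expected benefits of early discharge. A reader will want the size of that benefit with its uncertainty. The baseline scores must be collected to form the change, yet they improve precision only as far as subtraction allows, unless a baseline test happens to trigger adjustment. In a trial that already expects limited power for some secondary endpoints, that is an avoidable loss.

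**Working it through.** **Inputs from the article.** Sample size section: "Considering a 10% composite event rate", a margin of 10 percentage points, 80% power, a one-sided 97.5% interval, 5% loss and 298 patients. Intervention section: 1:1 allocation, stratified by need of cardiac surgery. Statistical analysis section: "All tests will be two-sided, and differences will be considered statistically significant at" 0.05.

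**Assumptions.** The article gives no SD, effect size or correlation for SF-12 or SPPB. I assume equal SDs at the two times and vary rho from 0.3 to 0.9.

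**Step 1: the stated sample size.** Per arm, 2 × 0.10 × 0.90 × (1.960 + 0.842)² / 0.10² = 141.28. In total 282.56, and 282.56 / 0.95 = 297.4, which rounds up to 298. The figure reproduces. Evaluable patients: 298 × 0.95 ≈ 283, or 141.5 per arm.

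**Step 2: what MANOVA means with one score at two times.** On one simulated data set (141 per arm), the group-by-time contrast from a MANOVA of baseline and 4-week score gave F = 18.047 on 1 and 280 degrees of freedom. The t-test on change gave t² = 18.047 and the same p-value. On this reading MANOVA is the change-score test.

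**Step 3: variances.** With common SD sigma:
- change score: 2(1 − rho) sigma²
- ANCOVA: (1 − rho²) sigma²
- ratio: (1 − rho²) / [2(1 − rho)] = (1 + rho)/2

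**Step 4: power.** Set the effect so that the change analysis has 80% power with 283 patients. This is a standardised difference in change of 0.334, with noncentrality 0.334² × 141.5/2 ≈ 7.9. ANCOVA has noncentrality 7.9 × 2/(1 + rho). A joint two-degree-of-freedom test on (baseline, week 4) has the same noncentrality as ANCOVA but one more numerator degree of freedom, because it also tests a baseline difference that randomisation makes null.

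| rho (assumed) | variance ratio | equivalent saving in N | change score | joint test (baseline, week 4) | ANCOVA |
|---|---|---|---|---|---|
| 0.3 | 0.65 | 35% | 80% | 88.4% | 93.5% |
| 0.5 | 0.75 | 25% | 80% | 83.2% | 89.9% |
| 0.7 | 0.85 | 15% | 80% | 78.0% | 86.0% |
| 0.8 | 0.90 | 10% | 80% | 75.5% | 84.0% |
| 0.9 | 0.95 | 5% | 80% | 73.1% | 82.0% |

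ANCOVA gains 13.5 points over change at rho 0.3, 9.9 at 0.5, 6.0 at 0.7 and 2.0 at 0.9. Over the joint test it gains 5 to 9 points across this range.

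**The case against.** **Direction.** A reader might infer that MANOVA cannot say which way the treatment works. The text does not support that. It says that mean change is compared, and step 2 shows that with two time points the contrast is the signed difference in mean change. The lack of a single signed effect applies only if a joint test is meant.

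**Baseline.** A reader might also infer that baseline is ignored. It is not: change subtracts it, and the imbalance rule may add it. What stands is that it is not a prespecified covariate. The gain from ANCOVA does not depend on imbalance, so that rule is no substitute.

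**Efficiency.** It is tempting to call MANOVA the least efficient option, or ANCOVA clearly superior throughout. Neither holds in general. The gain over change falls to 2 to 4 points at rho 0.8 to 0.9, and at rho 0.3 to 0.5 the joint test on (baseline, week 4) beats the change score. If SF-12 were analysed as two component scores, which the article never mentions, a joint test of their changes would have 95.2%, 88.4% or 83.2% power at between-component correlation 0, 0.3 or 0.5 when both move by the calibrated effect. That can match or exceed a single-score ANCOVA. If only one component moves, the figures are 70.7%, 75.0% and 83.2%.

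**Multiplicity.** Two separate SF-12 analyses, each at 0.05, are not comparable with one joint test at 0.05. This stands, and the fix has to deal with it.

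**Scope.** A journal article may leave the response vector and the reporting of intervals to the analysis plan. Those omissions alone would be no finding. But the article does name the method, for both endpoints, and that choice can be judged.

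**Conclusion.** The point holds as a recommended improvement to two secondary analyses. MANOVA is at best a change-score test under another name. As a joint test it gives no single signed effect and, for one score, has less power than ANCOVA. For a single score with equal SDs, ANCOVA is more precise than change at any rho below 1, apart from the one degree of freedom spent on the covariate. The gain is moderate at low to middling rho (about 10 power points at 0.5) and small at high rho (2 points at 0.9).

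The size rests on an assumed rho, equal SDs at both times, 283 evaluable patients and an effect calibrated to 80% power for change. The primary endpoint, the non-inferiority conclusion and the sample size of 298 are not touched.

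**What to change.** In the Statistical analysis section, replace MANOVA for both endpoints with a prespecified ANCOVA for each score: the 4-week score regressed on arm, the score at randomisation and the surgery stratum used in the randomisation. Report the adjusted mean difference with its 95% CI.

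State that the baseline score enters whatever the baseline comparison shows, so that the imbalance rule does not decide it. If SF-12 is reported as more than one summary score, name one as leading in advance or label all of them descriptive.

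Cost: wording only. Both scores are already needed to form the change, and the surgery stratum is known at randomisation. No extra data, visits or patients are required.
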